#### Costs in the secondary health care sector

The costs of secondary health care will be determined by Diagnostic Related Group (DRG) tariffs extracted from the National Patient Registry (NPR). The data include information on hospital departments, dates of admission and discharge, and diagnosis [50].

#### Costs in the primary health care sector

Data on the use of primary health care including contacts to general practitioners, medical specialists, and physiotherapists will be extracted from The Danish National Health Service Register for Primary Care (NHSR) and valued using the activity-based fees that are used to reimburse these providers. The NHSR contains information about the activities of health professionals’ contacts with the tax-funded public health care system [50].

#### Prescriptive medication

Data on the use of prescriptive medication will be extracted from the Danish National Register of Prescriptive Medication. This database includes information on all redeemed prescriptive medication and the associated costs.

#### Study participants’ out-of-pocket costs

Out-of-pocket costs such as non-prescriptive medication, dietary supplements, informal care, aids, and short term sick leave are assessed using a modified version of the Dutch cost diary [51]. The patient out-of-pocket costs will solely be included in the sensitivity analysis.

#### Productivity costs

This will be calculated using data on the number of weeks of sick leave obtained from the Danish Register for Evaluation of Marginalization (DREAM), which is administered by the Danish Ministry of Employment. This database includes information on all public transfer payments for all Danish citizens registered on a weekly basis since 1991 [52]. The productivity costs per study participant will be calculated using the Human Capital method [53]. Productivity costs will solely be included in the sensitivity analysis.

## Sample size

Two hundred and seventy two participants will be enrolled. The sample size calculation was based on the mean ADL motor ability as identified in the cross-sectional study to be 1.04 logits with a standard deviation (SD) of 0.727 logits [18]. For a two-sample *t*-test of normal distribution with a two-sided significance level of 0.05 and a common SD of 0.727, a sample size of 184 participants (92 per group) would provide 80 % power to detect a between-group difference of 0.3 logits [33]. To achieve this number, the study needs a total of 272 participants (136 per group), expecting a dropout rate based on previous studies of 32 % at 12 weeks follow-up [14, 16, 24, 54].

A sub-sample of ten participants will be recruited among the entire sample using purposive sampling for participant observations during intervention sessions and for qualitative interviews [48]. Specific criteria for selection will be defined prior to actual sampling.

## Data collection

Data will be collected at baseline (T1) by means of a study specific questionnaire (demography, health, cost diary, the IPA-DK, EORTC QLQ C-30, and the EQ-5D-5 L) and the One Day Diary. The questionnaire and the One Day Diary are sent out before a home visit by the P-OTs, where the AMPS and IPPA are applied, and a question about joyful activities and one about how they manage their everyday life are asked. In addition, data concerning use of assistive devices using a study specific questionnaire are collected. The two ADLs that the participant will perform for the AMPS observation are selected on basis of the One Day Diary and the IPPA data. See Fig. 1 and Table 1. The quality of AMPS data will be monitored by Center for Innovative OT Solutions, USA, and only valid data will be included.

**Fig. 1 Fig1:**
[figure not shown]
Randomisation and data collection

**Table 1 Tab1:** Schedule for collection of outcomes and cost data

Outcome	Source	Data collection method	Baseline T1	Week 6 T2	Week 12 T3	Week 24 T4
Everyday activities						
Quality of ADL performance	AMPS	Observation	X		X	
Problems with everyday activities	IPPA	Structured interview	X	X	X	
Autonomy and participation	IPA-DK	Questionnaire	X	X	X	
Health-related Quality of Life						
Health-related quality of life	EORTC QLQ C-30	Questionnaire	X	X	X	
Economic evaluation						
Quality Adjusted Life Years (QALY)	EQ-5D-5L	Questionnaire	X	X	X	X
Intervention costs		Questionnaire		X		
Costs in the secondary health care sector	The National Patient Registry	Register	X	X	X	X
Costs in the primary healthcare sector	The Danish National Health Service Register for Primary Care	Register	X	X	X	X
Prescriptive medication	Danish Register of Prescriptive Medication	Register	X	X	X	X
Out-of-pocket costs		Cost diary	X	X	X	X
Productivity costs	The Danish Register for Evaluation of Marginalization	Register and questionnaire	X	X	X	X

*AMPS* The Assessment of Motor and Process Skills, *EORTC QLQ-C30* The European Organization for Research Treatment of Cancer Quality of Life Questionnaire Core 30, *EQ-5D-5L* The EuroQol 5-dimensions 5 levels, *IPA-DK* The Danish version of the Impact on Participation and Autonomy Questionnaire (IPAQ), *PPA*, The Individually Prioritised Problems Assessment

There will be three follow-up occasions where cost data from registers are also extracted, while demographic data are only collected at T1:

T2) Six weeks after T1: a postal questionnaire identical to the one sent out at T1 and a study specific questionnaire on the type of interventions both groups have received and/or completed. Besides, an IPPA telephone interview is accomplished.

T3) 12 weeks after T1: identical to T1 except that a question whether their everyday life has improved is also asked.

T4) 24 weeks after baseline: a postal questionnaire that includes the cost diary and the EQ-5D-5L.

Observation based data are collected in conjunction with the intervention, and qualitative interviews with a subsample are accomplished at T3.

## Randomisation

Study participants will be randomly assigned to either the intervention group (receiving the Cancer Home-Life Intervention as a supplement to usual care) or the control group (receiving usual care and not receiving the Cancer Home-Life Intervention). See Fig. 1.

Randomisation will be carried out after T1 by an administration office, which is independent of the trial. Participants will be randomly assigned in a preset block size to either the intervention or control group with a 1:1 allocation by a computer-generated randomisation schedule. The block size will be kept unknown to all investigators and P-OTs and will not be revealed until the study has ended. The randomisation is stratified by centre.

## Blinding

Allocation is concealed to the study investigators. The P-OTs will also be sought blinded for the group allocation even though they may discover this when collecting follow-up data, and the study participants are told not to reveal their group allocation to the P-OTs during the follow-up occasions. At T3 the P-OTs will be asked to guess the group allocation of the participants. This may indicate if the blinding has succeeded. Allocation status cannot be blinded for the participants.

## Analysis

### Data analyses of the clinical evaluation

Scores will be calculated following the instructions in each instrument manual and presented by descriptive statistics. The intervention group will be compared with the control group by means of a multiple linear regression analysis in continuous data (AMPS, EORTC QLQ C-30 and IPPA), given the assumptions are fulfilled. If the assumptions are not met, a relevant transformation or logistic regression will be used. IPA-DK data are ordinal and will be dichotomised before logistic regression analysis is applied. The analysis of all outcomes will be adjusted for the stratification variable, centre. If there is significant imbalance between the two groups we shall consider adjusting for baseline ADL motor ability, baseline ADL process ability, gender, age, primary cancer diagnosis, education, employment and the EORTC QLQ-C30 global health status/quality of life in a sensitivity analysis [55, 56]. The between-group differences in continuous and dichotomised data will be presented with 95 % confidence intervals. A complete case analysis excluding participants without post-randomisation data will be performed [57]. It will be supplemented with a sensitivity analysis applying multiple imputation used to estimate a plausible value for the missing data of study participants lost to follow-up of other reasons than death [58].

Analyses will be performed to identify groups in which the Cancer Home-Life Intervention is especially effective. A subgroup-treatment effect interaction by a multiple regression analysis will be performed with the following possible variables as effect modifiers: age, gender, primary cancer diagnosis and WHO Performance score [59, 60].

*P* values ≤0.05 will be considered statistically significant. Analyses will be performed using STATA.

The One Day Diary data from T1 and T3 will be coded thematically into the following structure: 1) The activity domain comprising seven categories: self-care; care for others; household; leisure; transportation; procurement and preparation of food; and work. 2) The geographical domain: location and movements. 3) The social context: social circle and interaction. 4) The experiential domain: physical state and state of mind. The analyses will be used to describe the study participants’ daily activities with regard to each domain including duration and frequency of activities as well as activity patterns for the individual over the time of a day [47].

Field notes from the participant observations will be transcribed into a coherent text. Interviews will be transcribed verbatim. Both data sets will be analysed by thematic analysis to unfold and understand how the participants reacted to and experienced the usefulness of the received interventions, and to explore how the intervention worked and what aspects had particular relevance for the participants [48]. Thereafter, data derived from participant observations and interviews will be analysed with a constant comparative method. The analysis involves comparing different types of data from the two methods in order to systematically trace out categories and relationships within the data [61].

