#### Hypotheses

The quality of ADL performance as demonstrated by motor and process ability will be better in participants undergoing the Cancer Home-Life Intervention compared to participants who receive usual care.Participants undergoing the Cancer Home-Life Intervention will report less difficulty with prioritised everyday activities, better autonomy and participation, and higher levels of health-related quality of life compared to participants who receive usual care.The Cancer Home-Life intervention provides more Quality Adjusted Life Years (QALYs) at a higher incremental cost.The Cancer Home-Life intervention is cost-effective in a health sector perspective.

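### IPPA, IPA-DK and EORTC QLQ-C30 are measured at weeks 6 and 12, but their main analysis is a single-outcome, complete-case regression, so the week-12 estimate leaves out week-6 data from people lost in between

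*Protocol article*

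**What the plan says.** **Schedule.** In Table 1, AMPS is collected at T1 and T3 only. IPPA, IPA-DK and EORTC QLQ-C30 are collected at T1, T2 and T3. The text below the table confirms this: the T1 questionnaire is repeated by post at week 6, and for IPPA, "Besides, an IPPA telephone interview is accomplished".

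**Hypothesis.** The second hypothesis opens "Participants undergoing the Cancer Home-Life Intervention will report less difficulty with prioritised everyday activities" and goes on to autonomy, participation and quality of life. It names no visit.

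**Model.** Under Data analyses of the clinical evaluation: "The intervention group will be compared with the control group by means of a multiple linear regression analysis in continuous data". AMPS, EORTC QLQ-C30 and IPPA are listed together. IPA-DK is dichotomised and analysed by logistic regression. The adjustment fixed for all outcomes is centre. Some baseline variables may be added in a sensitivity analysis if the groups are imbalanced, but the T1 score of each scale is not part of the stated model. There is no term for visit, arm by visit, or correlation within a person.

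**Missing data.** "A complete case analysis excluding participants without post-randomisation data will be performed". Multiple imputation follows as a sensitivity analysis, restricted to participants lost for reasons other than death.

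**Expected loss.** The sample size section plans for 272 participants, "expecting a dropout rate based on previous studies of 32 % at 12 weeks follow-up". No figure is given for T2.

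**The concern.** A regression with one outcome per person is natural for AMPS, which has a single follow-up. Applied unchanged to scales with two follow-ups, it can use only one visit at a time. Someone who answers at week 6 and is lost by week 12 then adds nothing to the T3 estimate, although the trial holds a score for that person after most or all of the intervention.

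This matters more here than in most trials. A third of the sample is expected to be missing at T3, and the Discussion names mortality as a main difficulty. In such a population the T2 score is likely to be the best available predictor both of who is lost and of what they would have scored.

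At stake are the precision of the T3 contrast and its protection against selective loss in the headline result for every secondary clinical scale. The primary outcome is not affected.

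**Working it through.** **1. The plan's own figures.** With SD 0.727, difference 0.3, two-sided 0.05 and 80% power, n per arm = 2 × (0.727 × (1.960 + 0.842) / 0.3)² = 92.2, against the stated 92. Then 184 / 0.68 = 270.6, that is 271, or 272 as an even total. Both reproduce and are not in dispute.

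**2. Who is left out at T3.** Expected at T3: 272 × 0.68 = 185. T2 retention is not given, so it is assumed.

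| Assumed seen at T2 | n at T2 | Seen at T2, lost by T3 |
|---|---|---|
| 90% | 245 | 60 |
| 84% | 228 | 44 (19% of those seen at T2) |
| 75% | 204 | 19 |

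**3. Precision.** For a continuous scale under monotone loss, with T2-T3 correlation ρ, the variance of the T3 contrast using T2 values, relative to complete cases, is (1 − ρ²) + ρ² × n3/n2. Here n3/n2 = 0.68/0.84 = 0.81.

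| ρ (assumed) | Variance ratio | Reduction | Equivalent extra completers |
|---|---|---|---|
| 0.6 | 0.931 | 7% | 7% |
| 0.7 | 0.907 | 9% | 10% |
| 0.8 | 0.878 | 12% | 14% |

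Two qualifications apply.
- The comparison is with a T3 regression without the T1 score, as the plan states it. If both analyses carried the T1 score and all three visits were equally correlated, the relevant correlation would be ρ/(1 + ρ), that is 0.375 to 0.444. The gain from T2 alone would then be 0.375² × 0.19 to 0.444² × 0.19, about 3% to 4%.
- The table counts everyone lost after T2. If half of them had died and were not counted, n3/n2 would be 0.68/0.76 = 0.895 and the reduction 0.36 × 0.105 to 0.64 × 0.105, about 4% to 7%.

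For dichotomised IPA-DK the formula is only indicative.

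**4. Bias.** Large-sample simulation: true effect 0.40 SD at both visits, ρ = 0.7, and 19% loss after T2 depending on the T2 score, with poorer scores more likely to be lost (log-odds slope per SD as shown).

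| How loss depends on T2 score | Complete-case T3 effect | Using T2 values |
|---|---|---|
| Same slope and same loss rate in both arms, 0.5 to 1.5 | 0.40 | 0.40 |
| Same rule in both arms (so more loss in the poorer arm), 0.5 to 1.5 | 0.39 to 0.35 | 0.40 |
| Control arm only, slope 1 | 0.27 to 0.29 | 0.40 |
| Intervention arm only, slope 1 | 0.51 to 0.52 | 0.40 |

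The ranges in the last two rows depend on whether the overall loss rate is held equal between arms. The last column is an estimate that is valid under missing at random. Slopes, correlation and effect size are all assumptions.

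**The case against.** The strongest reply is that this is a condensed article, that an unnamed visit for secondary outcomes is usually settled in the analysis plan, and that the multiple imputation already planned does the same job. In the simulated setting, imputing T3 from T2 within arm gives 0.40, as a repeated-measures model does.

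Part of this stands. The unnamed visit alone would be only missing detail, and nothing stops the imputation from using T2. But the model and the main analysis set are stated, not deferred, and they fit a two-visit schedule badly. The imputation is a sensitivity analysis, so the headline result stays complete case. What is at issue is which analysis is the main one; a safeguard does exist.

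Three stronger readings are tempting, and the document does not support them.
- *Hypothesis 2 is tested at both visits.* Counting 1 IPPA score, 3 IPA-DK subscales and 15 EORTC scales twice would give 38 comparisons. The text does not say this: T2 alone, T3 alone and both all fit its wording.
- *A fading effect cannot be told from selective loss.* The plan poses no question about change in effect from T2 to T3 for these scales. Its interest in change over time concerns activity patterns. A substantial false change would also need loss that is informative differently by arm.
- *Complete cases understate the effect.* The direction is not fixed: the simulation gives values from 0.27 to 0.52 around a true 0.40.

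It is also right that a mixed model does not resolve death. Fitted without care, it carries scores past death, which the plan's own restriction on imputation avoids.

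**Conclusion.** The point holds as one of method. For the three secondary instruments with two follow-ups, the stated main analysis cannot use both, and it discards T2 values already collected from people lost before T3. Under the assumed 84% retention at T2 and correlation of 0.6 to 0.8, the cost is about 7% to 12% in the variance of the T3 contrast, and less if the T1 score is in both models or if many of those lost have died. Bias avoided under missing at random is near zero to 0.05 SD when loss is equally informative in the two arms. It reaches about 0.1 SD in either direction in the one-arm scenarios with slope 1.

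The size therefore rests on assumptions that the document neither supports nor rules out. The mismatch between schedule and model rests on the text alone. The outcomes are secondary, and the sample size and the AMPS analysis are unaffected. The change is worth making because it is cheap, but the trial's main conclusion does not depend on it.

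**What to change.** - For IPPA and each EORTC QLQ-C30 scale, make the main analysis one linear mixed model on T2 and T3 together, with arm, visit, arm by visit, centre and the T1 score of that scale, and unstructured covariance. For IPA-DK use the corresponding repeated-measures logistic or ordinal model.
- Name the T3 contrast, the visit of the primary outcome, as the one that decides hypothesis 2. Report T2 as supportive. IPPA is taken by telephone at T2 and at a home visit at T3, so a shift in its level between visits should not be read as change over time alone.
- State how deaths before T3 are treated, in line with the existing restriction of imputation to loss other than death, so that the model does not extrapolate scores past death.
- Keep the complete-case regression as a sensitivity analysis.

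The cost is analysis wording and somewhat more programming, with no new data and no further participants. The downside is that the main result then relies on missing at random for non-death loss.

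### If model assumptions fail, the primary outcome may move to a transformation or logistic regression, so the result would no longer be the 0.3 logit mean difference the trial is powered on

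*Protocol article*

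**What the plan says.** The Primary outcome section of the protocol article makes ADL motor ability from the AMPS the primary outcome. It describes this as a Rasch-converted linear measure in logits and gives 0.3 logits as a clinically relevant change. The Sample size section bases the trial on that scale, with "80 % power to detect a between-group difference of 0.3 logits".

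Under Data analyses of the clinical evaluation, AMPS, EORTC QLQ C-30 and IPPA are compared between groups by multiple linear regression, provided its assumptions hold. The next sentence reads: "If the assumptions are not met, a relevant transformation or logistic regression will be used". It makes no exception for the primary outcome.

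IPA-DK, a secondary outcome built from five-point items in three subscales, is treated differently and without any condition: "IPA-DK data are ordinal and will be dichotomised before logistic regression analysis is applied".

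**The concern.** The fallback sentence is a stated choice of method. It allows the primary result to be reported as a mean difference in logits, an effect on some transformed scale, or an odds ratio for being above a cut. Which of these is used would be settled by model checks on the trial data. Neither alternative can be read directly against the 0.3 logit difference that justifies the sample size, and logistic regression requires a continuous measure to be cut in two, which usually costs power.

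The switch is also poorly matched to the problem it is meant to solve. With about 92 analysed per group, non-normal residuals do little harm to a comparison of means, and unequal variances can be handled through the standard errors. A transformation is awkward too: with mean 1.04 and SD 0.727, and assuming normality, Φ(−1.04/0.727) = Φ(−1.43), or about 8% of scores, would lie below zero. There a log or square root is undefined without an arbitrary shift.

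For IPA-DK the text gives ordinality as the ground for dichotomising. Ordinality calls for an ordinal model; dichotomising discards category information and makes the result depend on the cut.

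**Working it through.** **Inputs (Sample size section).** "two-sided significance level of 0.05 and a common SD of 0.727"; ADL motor ability found "to be 1.04 logits with a standard deviation (SD) of 0.727 logits"; difference 0.3 logits; "a sample size of 184 participants (92 per group"); dropout 32%; "the study needs a total of 272 participants (136 per group").

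**1. The plan's own figures.**
- n per group = 2 × (1.960 + 0.842)² × 0.727² / 0.3² = 92.2, which rounds up to 93; stated 92.
- Standard error at 92 per group = 0.727 × √(2/92) = 0.1072. Power = Φ(0.3/0.1072 − 1.960) = Φ(0.839) = 79.9%; the exact two-sample t-test gives 79.5%.
- Enrolment = 184/0.68 = 270.6, so 271; stated 272.

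The plan's figures reproduce within rounding.

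**2. Power if the outcome is cut in two, normal data.** Assume the cross-sectional mean of 1.04 as the control mean, 1.34 in the intervention group, and SD 0.727 in both. For a cut c:
- p₀ = 1 − Φ((c − 1.04)/0.727) and p₁ = 1 − Φ((c − 1.34)/0.727)
- power = Φ((p₁ − p₀ − 1.960 × se₀)/se₁), where se₀ is the pooled and se₁ the unpooled standard error at 92 per group.

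No analysis cut is given, so a range is shown. The 2.0 value appears in the article only as the threshold for competent ADL performance; 1.19 is the midpoint of the two means.

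| Cut (logits) | p₀ | p₁ | Power at 92 per group |
|---|---|---|---|
| 0.5 | 77.1% | 87.6% | 46% |
| 1.19 | 41.8% | 58.2% | 60% |
| 1.5 | 26.3% | 41.3% | 57% |
| 2.0 | 9.3% | 18.2% | 41% |

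For c = 1.19: (0.1635 − 1.960 × 0.0737)/0.0727 = 0.26, and Φ(0.26) = 60%. For c = 2.0: (0.0886 − 1.960 × 0.0508)/0.0504 = −0.22, and Φ(−0.22) = 41%. Restoring 80% power would take 146 per group (292 evaluable) at 1.19 and 236 per group (472 evaluable) at 2.0, against 184 planned.

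**3. The same comparison with skewed data.** The fallback would be triggered by data that do not fit the model, so normal data are not the natural test case. Simulated gamma outcomes with control mean 1.04, SD 0.727, a shift of 0.3 and 92 per group (20,000 data sets) give approximately:

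| Skewness | t-test power | t-test type I error | Split at pooled median | Cut at 2.0 |
|---|---|---|---|---|
| 1 | 80% | 5% | 67% | 25% |
| 2 | 80% | 5% | 80% | 18% |

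The mean comparison keeps both its error rate and its power under marked skewness. The dichotomised comparison ranges from no material loss to losing most of the power.

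**4. Transformation branch.** No power figure is calculated for it. It alters the scale of the effect but need not discard much information.

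**5. IPA-DK.** The article gives no distribution, expected effect, cut or power for this outcome, so nothing can be computed.

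**The case against.** The default analysis is already the right one: linear regression on logits. The fallback is conditional, and a damaging violation is not especially likely for a Rasch-based linear measure. The sentence also serves EORTC QLQ C-30, whose single-item scales are bounded at 0 to 100 and where another model is less odd. The economic evaluation presents clinical outcome means with bootstrapped intervals and uses ADL motor ability as its clinical parameter, so a logit-scale mean would still be reported. Triggers, transformations and cut-points normally belong in a statistical analysis plan, which is not shown.

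Much of this stands, and it rules out several stronger readings:
- A reader might infer that the plan abandons the powered effect. It does so only if the fallback is used.
- A reader might infer that any use of the fallback forfeits the 80% power. That does not follow for a transformation.
- A reader might take 60% and 41% as the expected power after a switch. They assume normal data, for which a normality check would not usually trigger the switch.
- A reader might carry the same loss over to IPA-DK. The article offers no figures for that, and IPA-DK is neither in logits nor part of the power calculation.
- The absence of a trigger or cut from a condensed article is not itself a fault.

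What the objection does not remove is that the article expressly permits logistic regression or a transformation for the primary outcome. An analysis plan that filled in the details would still be working within that permission. The means in the economic evaluation do not settle which analysis is the primary test.

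**Conclusion.** The point holds in a limited form. The primary effect measure is open to a data-dependent change away from the 0.3 logit mean difference behind the sample size, and the change is unnecessary because the mean comparison is robust at this sample size. If the logistic branch were used, power could fall substantially: to between 41% and 60% over cuts from 0.5 to 2.0 logits under normality, and to anywhere from about 18% to about 80% in the skewed examples. These are illustrations. They rest on a pure 0.3 logit shift, the cross-sectional mean as control mean, 92 analysed per group, no adjustment for centre, and cuts chosen here because the article states none.

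The dichotomised IPA-DK analysis is a separate and lesser weakness in a secondary outcome. Its direction is clear, but its size cannot be determined from the article.

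**What to change.** For the primary outcome, state that the between-group mean difference in ADL motor ability, in logits and from the linear model adjusted for centre, is the primary analysis in all circumstances. If residuals are non-normal or variances unequal, keep that estimate and use robust standard errors or bootstrap confidence intervals; the economic evaluation already uses bootstrapping. Remove the transformation and logistic options for this outcome.

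For IPA-DK, make an ordinal regression adjusted for centre the main analysis and show the dichotomised result descriptively.

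The cost is wording only, with no extra participants or data. The small downsides are the proportional-odds assumption for IPA-DK and an odds ratio that is slightly harder to explain; showing proportions alongside helps with the second.

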## Instrumentation

### Primary outcome

Quality of ADL performance is measured by *The Assessment of Motor and Process Skills (AMPS)* [33]. The AMPS is a standardised, observation-based assessment designed to evaluate the quality of a person’s ADL performance regarding ease, efficiency, safety, and independence. A trained and calibrated P-OT observes the quality of 16 motor and 20 process performance skills (ADL ability) while the person performs two familiar and relevant ADLs, and rates the person’s performance of each skill on a four-point ordinal scale. The ADL motor ability is a measure of how much physical effort, clumsiness, and/or fatigue the person demonstrates during ADL performance. The ADL process ability is the person’s overall efficiency regarding appropriate use of time, space, and objects throughout ADL performance. The ordinal scores are converted into two overall linear ability measures by Rasch-based computer-scoring software: one for ADL motor ability and one for ADL process ability expressed in logistically transformed probability units (logits). The two overall linear ability measures are adjusted for task challenge, skill item difficulty, and rater severity. ADL motor ability above 2.0 logits and ADL process ability above 1.0 logits indicate competent ADL performance, and 0.3 logits a clinical relevant change [33]. In the present study, the ADL motor ability is used as the primary outcome. The P-OT also assesses the five most effective and the five most ineffective ADL motor and process skills based on clinical reasoning [33]. The AMPS has been found valid and reliable in people with advanced cancer [34, 35] and responsive in people with other disorders [33].

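### The main analysis adjusts for centre only and leaves baseline ADL motor ability to an imbalance-triggered sensitivity analysis, giving up precision and some robustness that the T1 data already offer

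*Protocol article*

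**What the plan says.** The section *Primary outcome* names the endpoint: "In the present study, the ADL motor ability is used as the primary outcome". Table 1 schedules AMPS at T1 and T3, so every randomised participant should have a baseline value. Randomisation is stratified by centre alone, so baseline ability is not balanced by design.

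The section *Data analyses of the clinical evaluation* plans a multiple linear regression for AMPS and fixes one covariate: "The analysis of all outcomes will be adjusted for the stratification variable, centre". Baseline ability comes next, as a possibility: "If there is significant imbalance between the two groups we shall consider adjusting for baseline ADL motor ability". It heads a list of eight covariates, and the sentence ends by placing that adjustment in a sensitivity analysis. The main analysis set is complete cases. Multiple imputation is a further sensitivity analysis, restricted to losses other than death.

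The section *Sample size* uses an unadjusted two-sample t-test "with a two-sided significance level of 0.05 and a common SD of 0.727" and states that "a sample size of 184 participants (92 per group) would provide" 80% power for 0.3 logits. Enrolment is raised to 272 for an expected 32% dropout at week 12. No section puts baseline AMPS in the main model.

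**The concern.** A baseline measurement of the outcome reduces residual variance in proportion to its squared correlation with follow-up. That benefit exists whether or not the arms happen to differ at baseline, so an imbalance trigger asks the wrong question. If the trigger means a significance test, it tests a hypothesis that randomisation makes true, and it passes over chance differences large enough to matter for the estimate. The wording adds discretion, since the adjustment is only to be considered.

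There is a second, conditional issue. About a third of participants are expected to be lost, and the main analysis uses complete cases. If loss selects on baseline ability differently in the two arms, the completers are no longer comparable at baseline, and a model without baseline carries that difference into the estimate. At stake are the precision of the primary comparison and, under that condition, its bias and type I error.

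**Working it through.** **Inputs from the article.** SD 0.727 logits, from a single cross-sectional measurement; difference 0.3 logits; two-sided alpha 0.05; 92 evaluable and 136 enrolled per group; 32% dropout.

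**Assumptions, not in the article.** The baseline-to-T3 correlation r, shown from 0.3 to 0.7. The dependence of dropout on baseline, taken as a logistic slope per baseline SD, with 32% loss in each arm.

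**1. The plan's own figure.** n per group = 2(1.960 + 0.842)² × 0.727² / 0.3² = 92.2. The exact t-test gives 79.5% power at 92 per group and 79.9% at 93. Inflation: 92 / 0.68 = 135.3, so 136 per group and 272 in all. The stated numbers reproduce.

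**2. Power with baseline in the model.** Residual SD = 0.727 × √(1 − r²), put into the same noncentral t at 92 per group:

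| r | Residual SD | Power | Equivalent unadjusted n per group, 92/(1 − r²) |
|---|---|---|---|
| none (centre only) | 0.727 | 79.5% | 92 |
| 0.3 | 0.694 | 83% | 101 |
| 0.5 | 0.630 | 90% | 123 |
| 0.6 | 0.582 | 94% | 144 |
| 0.7 | 0.519 | 97% | 180 |

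**3. What the trigger lets through.** With 92 completers per group, the SE of a baseline difference is 0.727 × √(2/92) = 0.107 logits. A two-sided 5% test does not flag differences below 1.96 × 0.107 = 0.21. Given an observed baseline difference D, the expected shift in the unadjusted T3 difference is r × D. At D = 0.21 this is 0.105 (r = 0.5), 0.126 (r = 0.6) and 0.147 (r = 0.7), or 35% to 49% of the 0.3 target.

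**4. Dropout, true effect zero.** The bias of the unadjusted complete-case estimate is r × 0.727 × (difference between arms in the completers' mean standardised baseline).

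| Slopes, arm 1 / arm 2 | Completers' mean baseline (SD units) | Bias at r = 0.3 | r = 0.5 | r = 0.7 |
|---|---|---|---|---|
| −0.7 / −0.7 | 0.204 / 0.204 | 0 | 0 | 0 |
| −0.7 / 0 | 0.204 / 0 | 0.044 | 0.074 | 0.104 |
| −1 / 0 | 0.269 / 0 | 0.059 | 0.098 | 0.137 |
| −1 / −0.3 | 0.269 / 0.094 | 0.038 | 0.063 | 0.089 |

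Simulation (136 per arm, 4,000 trials per scenario, r = 0.5 and 0.7) agrees. In the three unequal scenarios, type I error without baseline was 9% to 15% at r = 0.5 and 13% to 24% at r = 0.7. With baseline in the model, bias was about 0 and type I error about 5%. The sign of the bias depends on which arm loses more low-ability participants.

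**The case against.** The design and the analysis agree with each other. The trial was sized on an unadjusted test and keeps about 80% power under one. This stands: what is lost is precision, not planned power, and its amount depends on a correlation that the article does not give. At r = 0.3 the gain is only about 4 percentage points.

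A reader might infer that the imbalance rule makes the primary test data-dependent. It does not. The primary covariate set is fixed in advance as centre, and the trigger governs only a sensitivity model. Missing data apart, the centre-adjusted test keeps its type I error over repeated randomisations. The article also names no balance test, so the trigger could mean a substantial difference and not a formally significant one; step 3 takes the formal reading.

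A reader might also infer that the complete-case estimate is biased whenever loss is related to prognosis. The first row of the second table shows otherwise: equal dependence in both arms gives no bias. The article reports no arm-specific dropout pattern. One is possible, since participants are unblinded and only one arm receives the home visits and calls of the intervention, but that is conjecture.

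The planned multiple imputation bears on the same risk. It softens the point without removing it, because it is secondary, leaves out deaths, and its imputation variables are not listed.

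Finally, the article does not say whether AMPS is analysed as the T3 value or as change. A change score would already use baseline, and the figures above would not apply as they stand. The single-measurement SD in the sample size points to the T3 value. A change score would in any case be less efficient than baseline adjustment: at 92 per group its power is 65%, 79.5% and 95% at r = 0.3, 0.5 and 0.7.

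**Conclusion.** The point holds as an improvement in efficiency and robustness, not as an error in the stated design. Leaving baseline ADL motor ability out of the main model forgoes roughly 4 to 18 percentage points of power for r between 0.3 and 0.7. It also leaves chance baseline differences too small to trip the trigger free to move the estimate by up to 0.11 to 0.15 logits at r of 0.5 to 0.7.

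The bias of about 0.04 to 0.14 logits arises only if the link between baseline and dropout differs by arm. Baseline adjustment removes that part and no more. It does not deal with loss driven by decline after baseline, or with death, which the article's Discussion names as a challenge in this population.

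**What to change.** State the primary analysis as a linear regression of T3 ADL motor ability on treatment, centre and baseline ADL motor ability, whatever the observed balance. Adjust each other continuous outcome (ADL process ability, IPPA, EORTC QLQ-C30) for centre and its own baseline. If baseline is added to the logistic model for dichotomised IPA-DK, report the odds ratio as conditional on baseline, because it then estimates a different quantity from the centre-adjusted one. Delete the imbalance trigger, and keep the remaining listed covariates as one fixed sensitivity model. Include baseline ADL motor ability in the imputation model.

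The cost is a change of wording before unblinding. AMPS, IPPA, IPA-DK and QLQ-C30 are all scheduled at T1, so no new data are needed, and the sample size can stay as it is.
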